### Intervention

The BCPPA intervention^29^ was refined to be delivered online via telehealth in four stages over four to six 1-hour sessions for the purposes of this study (BCPPA and other rare dementias). The prior BCPPA intervention was designed to be delivered face to face over four 1-hour sessions for pragmatic reasons.^28^ Given little is known about the optimal dose of BCPPA, the current study aims to explore the dosage implementation by delivering the intervention over 4–6 sessions. Total number of sessions will be jointly decided by the person with PPA, their CP and the treating SLT, based on their progress in the intervention. People with PPA and their CPs will attend all sessions together. Sessions will be facilitated by the RA or local collaborator SLT via Zoom. Video samples will be made by the participants between the two baseline assessments (to ensure naturalness) prior to intervention. From these recordings, the SLT will assess the dyad’s communication and conversation strengths and needs before commencing the programme. A full description of the BC intervention used in this study is provided in the TiDIER documents (online supplemental appendix).

### Deferred entry group

Participants randomised to the deferred entry group will not receive speech and language therapy for a 6-week period prior to the deferred start of the BCPPA intervention. At present, speech and language therapy services are typically unable to deliver prompt or, in many cases, services for people with dementia who have communication difficulties.^36–38^ Thus, the deferred entry comparator group provides a control condition comparable to a waiting list in an NHS setting.

For the entirety of their participation in the study, both groups will receive all other usual healthcare provision (anticipated to include neurology/psychiatry in dementia diagnostic clinics, general practitioner (GP) reviews and allied health input such as physiotherapy). However, this will exclude any other speech and language therapy interventions until after the 3-month follow-up appointment. At this point, participants will be able to resume all aspects of speech and language therapy provision.

### Allocation concealment and masking

The RA, local collaborators and participants will be masked to treatment allocation during the pre-intervention outcome measures, and outcome assessors administering post-intervention outcome measures will also be masked to allocation. Only single masking will be implemented, as it is not feasible with this and other behavioural interventions to mask the RA or local collaborator delivering the intervention. Participants will be asked not to tell the outcome assessors whether they have had the intervention or not. Outcome assessors will be asked to keep a log of whether they believe they have been unmasked and will receive guidance and training from the RA on how to remain masked.

### Assessment of fidelity

As per gold standard in measurement of treatment fidelity,^39^ all assessment and intervention sessions will be video recorded. At the end of the trial, a random sample of 20% of viable recordings will be analysed using an intervention adherence checklist. Two independent raters will code for adherence to core intervention components and evaluate inter-rater reliability. Consensus methods will be employed where differences are identified. The RA and local collaborators will also be asked to reflect on intervention adherence by completing reflective logs following each session, including documenting session length and tasks completed.

### Assessment of acceptability of the intervention

To inform our understanding of acceptability, anonymised information about diagnosis, time since symptom onset and reason for exclusion will be documented for all potential participants who are not eligible or decline to participate. Acceptability itself will be measured via session attendance and dropout rates, as well as through qualitative feedback from semi-structured interviews. Participating dyads and healthcare professionals delivering the intervention will be invited to participate in semi-structured interviews before and after involvement in the trial. While participants in the current trial will be unable to compare online receipt of the intervention with in-person receipt, a previous pilot study revealed that face-to-face BCPPA was acceptable to participants;^29^ thus, the aim of the current pilot is to determine acceptability of online delivery before proceeding to full trial. The interview topic guide has been informed by the Promoting Action on Research Implementation in Health Services framework^40^ (online supplemental appendix).

### Technical screen and support

A technical screen will be administered during the first baseline session, face-to-face in the participants’ home. This will allow for an assessment of internet functionality and ensure that participants can use Zoom on their own or a loaned device. The technical screen will assess how well dyads can jointly open their device, access a Zoom link and operate the microphone and camera functions. Participant dyads will be asked to navigate the telehealth technology three times with systematic prompts. A measure of responsiveness to prompts will be recorded as time taken and number of prompts required (see online supplemental appendix for the tech screen document). Participants who are unable to navigate the telehealth technology on at least one of the three occasions will be excluded from the study. Additionally, participants will receive information to support access to future remote sessions on Zoom in the form of a co-designed, aphasia-friendly, two-page instruction manual. This was developed in collaboration with the BCPPA and other rare dementias PPI advisory group, detailing how to join and navigate therapy session via Zoom on laptops and iPads. This easy-to-follow manual has also been adapted as a closed caption YouTube video.

### Outcome measures

Outcome measures will be collected at four or five time points depending on randomisation. All participants will complete baseline measures on two occasions prior to randomisation to monitor stability. Participants randomised to the immediate intervention condition will complete measures immediately after the intervention and 3 months after receiving the intervention (ie, four times). After completing the two baseline measure sessions, the deferred group will complete the outcome measures again before, immediately after and 3 months after intervention (ie, five times). Table 2 provides an outline for participants’ schedule of involvement including enrolment, intervention and outcome measurement.

**Table 2 T2:** Schedule of enrolment, interventions and outcome measures

Timepoint	Trial period						
	Enrolment			Post-randomisation			Close-out
	*-t_i_* to 0	*t_1_* *Baseline*	*t_2_* *Baseline*	*t_3_* *Post-treatment/ deferral waiting period*	*t_4_** *Deferred entry group post-treatment only*	*t_5_* *12 week post-intervention follow-up*	*t_x_*
Enrolment							
Eligibility screen	X						
Informed consent		X					
Baseline assessments		X	X				
Randomisation			X				
Intervention/comparator							
*BCPPA*							
*Deferred entry group*							
Assessments							
Primary outcome (*CCRSA*)		X	X	X	X*	X	
Primary outcome (*CPIB*)		X	X	X	X*	X	
Secondary outcome (*CAT subtests*)				X	X*		
Secondary outcome (c*onversation samples*)		X	X	X	X*	X	
Secondary outcome (*GAS*)		X	X	X†	X†	X	
Secondary outcome (*personal narrative*)		X	X	X	X*	X	
Secondary outcome (*picture description*)		X	X	X	X*	X	
Secondary outcome (*PACT*)		X	X	X	X*	X	
Secondary outcome (*QCPR*)		X	X	X	X*	X	
Health economics (*EQ5-5D-5L+C*)		X	X	X	X*	X	
Health economics (*ICECAP-O*)		X	X	X	X*	X	
Health economics (*RUD*)		X		X			
Semi-structured interviews			X				X

* Deferred entry group assessment only.

† Completed as part of the intervention in both conditions (ie, immediate treatment and deferred entry group).

BCPPA, Better Conversations with Primary Progressive Aphasia; CAT, Comprehensive Aphasia Test; CCRSA, Communication Confidence Rating Scale for Aphasia; CPIB, Communicative Participation Item Bank; EQ5-5D-5L+C, EuroQol 5-Dimension 5-Level questionnaire plus Cognition; GAS, Goal Attainment Scaling; ICECAP-O, Investigating Choice Experiments for the Preferences of Older People; PACT, Progressive Aphasia Communication Tool; QCPR, Quality of the Carer-Patient Relationship Scale; RUD, Resource Utilisation in Dementia; t_x_, testing timepoints.

The combined time for completing the measures should not exceed 90 min, including greetings, rapport building, technical set-up and switching between tests. Pre-intervention measures will be administered by the RA or a local SLT collaborator, while all post-intervention or deferred entry period and 3-month follow-up measures will be administered by an outcome assessor (an SLT student with training in the assessment of people with PPA and dementia) but crucially masked to treatment group allocation (immediate or deferred entry group).

During the BCPPA intervention, participant dyads will also complete Goal Attainment Scaling^41^ to determine specific individualised targets for the intervention and measure change in these targets. With support from the SLT, participant dyads will identify goals and weigh the goals according to their importance and likelihood of being achieved. At the end of therapy, the goals will be reviewed by the participant dyads with the support of an SLT and an outcome score agreed.

Outcome measurement tools described in table 3 were selected based on a recent international core outcome set for PPA.^18^ To capture the top construct from the core outcome set for PPA (*participate in conversations with family and friends)*, two primary outcome measures were selected: the Communication Confidence Rating Scale for Aphasia (CCRSA)^42^ and the Communication Participation Item Bank (CPIB).^43^ The CCRSA captures participants’ confidence in communication activities including conversations, whereas the CPIB captures participants’ ratings of their ability to participate in conversations. The CCRSA has been shown to demonstrate change in confidence over time in previous PPA intervention studies (eg, ^44–46^) including the prior BCPPA pilot study.^29^ However, the CCRSA has only been validated for people with stroke aphasia,^42^ and there are no published psychometric studies on its use in PPA. The CPIB has also been used in previous PPA intervention studies.^44
45^

**Table 3 T3:** List of outcome measures and their alignment with the core outcome set for PPA constructs^18^

Measure	Description	Approximate administration time and to whom	Alignment with the COS PPA constructs
Primary outcome measures			
Communication Confidence Rating Scale for Aphasia (CCRSA)^42^	A 10-item questionnaire whereby the participant rates their confidence on a Likert scale from 0 to 100	15 min; person with dementia only	Participate in conversations with family and friends
Communication Participation Item Bank (CPIB)^43^	Communication Participation Item Bank (CPIB)^43^	10 min; person with dementia only	Participate in conversations with family and friends
Secondary outcome measures			
Comprehensive Aphasia Test (CAT)^47^	Three language subtests comprising spoken sentence comprehension, spoken object naming and picture description subtests	15 min; person with dementia only	Get words out, be more fluent and understand what others are saying
Personal narrative	Talking on a topic of interest elicited with *“*Tell me about something that is personally meaningful to you*”* with examples and prompts	5 min; person with dementia only	Get words out and be more fluent
Conversation samples	In the first assessment session, participants will be recorded having a 10 min (approximately) conversation. Participants will then make three 10 min video recordings of natural conversation using a loaned iPad and stand before the second assessment. This will be repeated at all other assessment timepoints.	10 min; both the person with dementia and their communication partners	Participate in conversations with family and friends and convey a message by any means
Progressive Aphasia Communication Toolkit (PACT)^52^	PACT ratings are done by an independent assessor, masked to timepoint, based on video-recorded discourse and conversation samples.	No additional minutes. PACT ratings are done by an independent assessor, masked to timepoint, based on video-recorded discourse and conversation samples of the person with dementia.	Get words out, be more fluent, convey a message by any means and understand what others are saying.
Goal Attainment Scaling (GAS)^41^	GAS is completed during the intervention itself and reviewed at the end to determine specific individualised targets for the intervention and measure change in these targets.	No additional minutes; both person with dementia and their communication partners	
Quality of caregiver-patient relationship (QCPR)^53^	A questionnaire designed to evaluate relationship and completed by both the person with dementia and their carer. The rating scale requires participants to rate 14 statements on a 1–5 scale from totally agree to totally disagree.	10 min; both person with dementia and their communication partners	

COS PPA, core outcome set for primary progressive aphasia.

Additional secondary outcome measures were selected to understand the impact of the intervention on language and discourse skills. These were the spoken-sentence comprehension, spoken-object naming and picture-description subtests from the Comprehensive Aphasia Test (CAT).^47^ A personal narrative was identified as the most valid elicitation task for generating spoken-discourse samples in best practice guidelines for reporting spoken discourse in neurogenic communication disorders.^48^ It is also identified as one of the most ecological and functional methods of evaluating discourse in a systematic review of discourse measures.^49^ A personal narrative also provides a more naturalistic, less constrained discourse sample to contrast with the highly structured and constrained sample collected via the CAT picture-description task.

Conversation samples were selected as further secondary outcomes measures both to enable the measurement of change in conversation behaviours (both in the person with dementia and their CPs) and as the most proximal measure to the BCPPA intervention. Video recordings of natural conversations between the person with dementia and their CPs will be coded by raters masked to pre-intervention/post-intervention timepoints. They will identify and count conversation behaviours using an approach developed for use in BC intervention studies^50^ and previously used in the BCPPA study.^29^ Given the time-consuming nature of this outcome measure, a comparable clinical measure, the Kagan Measure of Skill in Conversation–Dementia and Measure of Participation in Conversation–Dementia Scale,^51^ will also be used for comparison. Video recordings will also be used for masked assessors to administer the Progressive Aphasia Communication Toolkit (PACT).^52^ PACT is designed for people living with conditions that result in progressive communication change, such as dementia and PPA. PACT documents and monitors symptom progression or treatment responsiveness using qualitative report and scales that evaluate strengths and needs across the communication domains: speech-voice, language, social-pragmatics and discourse.

Quality of caregiver–patient relationship^53^ measures change in both participants’ relationship to one another. Relationship was identified by the PPI advisory group as an important domain to consider.

### Process evaluation

Following the intervention, participants with dementia and their CPs will be asked to participate in semi-structured interviews, structured using the Normalisation Process Theory,^54
55^ to capture perceived barriers and facilitators for future implementation (see topic guide in online supplemental appendix). All healthcare professionals involved in referring people with dementia to the study or delivering the intervention themselves (local SLT collaborators) will also be asked to participate in the interviews, also structured using the Normalisation Process Theory, to capture perceived barriers and facilitators for future implementation (see draft topic guide in online supplemental appendix). These interviews will be conducted after they have delivered the intervention and will be conducted on Zoom, lasting for up to 90 min.

### Health economic evaluation

The health economic analysis will determine the most appropriate perspective of analysis and methods of measuring and valuing costs and outcomes in a future cost-effectiveness analysis of BCPPA versus usual care. The Health Economics Analysis Plan (HEAP) will set outline objectives and methods for data collection and analysis, and data will not be shared with the health economics researchers until the HEAP has been reviewed and approved by the lead health economist (co-author [name]). To explore the feasibility of adopting both a health and social care perspective and wider societal perspective, we will collect data using the EuroQol 5-Dimension 5-Level^56^ to derive quality-adjusted life years, the Investigating Choice Experiments for the Preferences of Older People ^57^ to capture wider capability-based quality of life, and a validated questionnaire, the Resource Utilisation in Dementia^58^ to capture service utilisation costs (see table 4 for a summary of health economic measures). The economic analysis will explore the completeness and responsiveness of the health economic measures to inform the design of a future definitive cost-effectiveness analysis.

**Table 4 T4:** List of health economic measures

Health economics measures		
Measure	Description	Approximate administration time
EQ5-5D-5L+C^56^ A brief health-related quality-of-life measure with cognition.	A 6-item questionnaire designed to evaluate health-related quality of life. This will be completed by both the person with dementia and their partners.	5 min/person
Investigating Choice Experiments for the Preferences of Older People - CAPability index (ICECAP-O)^57^ Has been identified as the health economic measure that most closely aligns with the constructs identified on the core outcome set for PPA.^18^ Has been used in previous speech and language conversation intervention studies^66^	A 10-item questionnaire designed to evaluate capability. This will be completed by both the person with dementia and their partners.	5 min/person
Resource utilisation in dementia (RUD)^58^ questionnaire The RUD is a validated instrument for assessing resource use (community and hospital-based resource use).	A questionnaire asking the participant to outline the number of healthcare contacts and service use (eg, admissions/GP appointments) over a set time period. To be completed by the carer only, this measure captures service use of both the person with dementia and their carer.	15 min

GP, general practitioner.

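### The masked assessor is assigned the RUD at t3, and this form on healthcare contacts could reveal the arm: an avoidable unmasking risk

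*Protocol article*

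**What the plan says.** Under Outcome measures, "all post-intervention or deferred entry period and 3-month follow-up measures will be administered by an outcome assessor", and that assessor is "crucially masked to treatment group allocation (immediate or deferred entry group". No exception is made for the health economic measures. In Table 2 the RUD is marked at t1 and t3 only, so t3 is its single use after randomisation.

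Table 4 (Health economic evaluation) describes the RUD as "A questionnaire asking the participant to outline the number of healthcare contacts and service use (eg, admissions/GP appointments) over a set time period", and adds: "To be completed by the carer only, this measure captures service use of both the person with dementia and their carer". Its allotted time is 15 minutes.

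Under Allocation concealment and masking, "Participants will be asked not to tell the outcome assessors whether they have had the intervention or not". The same section provides assessor guidance and training, and "Outcome assessors will be asked to keep a log of whether they believe they have been unmasked".

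The Intervention section sets 4 to 6 one-hour sessions. The Deferred entry group section withholds speech and language therapy from the deferred arm for 6 weeks. It also says of usual care in both arms that "this will exclude any other speech and language therapy interventions until after the 3-month follow-up appointment".

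**The concern.** Dyads are asked to keep the intervention from the assessor. At the same visit the assessor is assigned a form that asks the carer which healthcare contacts the dyad has had. If the trial sessions count as such contacts and the assessor sees the answers, the form asks for what the carer was told to withhold.

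The timing matters. The analysis plan compares immediate with deferred entry before and after therapy, and t3 is the one visit at which a treated arm can be set against an untreated one. The t4 visit exists only for the deferred arm, so attending it already identifies the arm, and by the 12-week follow-up both arms have been treated. An assessor who learns the arm at t3 could, without intending it, change how much support or prompting a person with language impairment receives.

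**Working it through.** No sample size, power or error-rate figure is involved, so the check sets the provisions side by side.

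**1. Who gives the RUD at t3?** Outcome measures assigns all post-intervention and deferral-period measures to the masked assessor, and Table 2 marks the RUD at t3. Read as written, the masked assessor gives it.

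**2. Would the answer differ by arm?** Speech and language therapy contacts between randomisation and t3:

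| Arm | Trial sessions | Other speech and language therapy | Total |
|---|---|---|---|
| Immediate | 4 to 6 | barred | 4 to 6 |
| Deferred | 0 | barred | 0 |

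Any such contact in this interval should therefore be a trial session. A report of none is also informative. One qualification is that the recall period is given only as a set time. If it reaches back before randomisation, earlier contacts could appear in either arm and blur the contrast.

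**3. Does the RUD ask for trial sessions?** The protocol does not say. The examples are admissions and GP appointments, but they are only examples. The sessions are delivered by registered speech and language therapists, one site is a speech and language therapy service, and the RUD is there to capture service use. A carer could reasonably list the sessions, and nothing tells them not to.

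**4. Would the assessor see the answer?** This is also unstated. The carer completes the form, but whether it is self-completed or read out, where it falls in the visit and who receives it are not given.

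**5. The possible cases:**

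- Trial sessions excluded, or form unseen by the assessor: the RUD need not reveal the arm, and the number unmasked by it could be 0.
- Trial sessions reported and form seen: the answer nearly identifies the arm for every dyad that answers fully, up to the 36 planned.

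The document does not place the trial between these limits.

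**6. Which outcomes could be affected?**

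- CCRSA and CPIB (co-primary): rated by the person with dementia, who knows the allocation. Any bias from that knowledge exists whatever the assessor knows, so the added exposure is limited to how the questionnaires are administered.
- Conversation samples and PACT: rated from video by raters masked to timepoint. The visit assessor does not score them.
- Comprehensive Aphasia Test subtests (including picture description) and personal narrative: administered or elicited in person, the narrative with examples and prompts. This is the main exposure. Altered prompting could carry into PACT, which is rated partly from recorded discourse.

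**The case against.** The strongest reply is that the key step is an inference. The protocol nowhere says that trial sessions go on the RUD or that the assessor sees the form. Completion by the carer is compatible with self-completion. The word all in the assignment rule is not literal either: Goal Attainment Scaling is marked at t3 but done within the intervention, and PACT is rated from video by someone else. Mode, recall period and routing may be settled in the Health Economics Analysis Plan, which the article says will cover data collection and which is not shown. Assessor training is a stated preventive measure, and the log gives a further check.

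Much of this stands. A reader might infer that masking is broken at t3, or put a count on the dyads unmasked. The documents support neither, because any count needs a disclosure rate that they do not give. A reader might also infer that assessor masking is the only masking after baseline, so that the primary outcomes are compromised. That is wrong, because the video raters are masked to timepoint and both primary outcomes are self-ratings.

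What does not stand is that the matter is only missing detail. Who gives the t3 measures and how masking is kept are rules fixed in this article, and followed as printed they pull against each other. Training does not stop a carer answering a form truthfully, and the log records unmasking after it has happened.

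**Conclusion.** The point holds as an avoidable unmasking risk at the visit carrying the randomised comparison. The contrast a full answer could expose is 4 to 6 speech and language therapy contacts against 0. Whether it reaches the assessor rests on two unstated matters: whether trial sessions are reported on the RUD, and whether the assessor sees or hears the answers. The likely effect is confined mainly to administration and prompting of secondary language and discourse measures. It does not threaten the feasibility aims. It merits correction because the change is specific and nearly free.

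**What to change.** Amend Allocation concealment and masking, and the assignment rule under Outcome measures, in one of two ways:

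- **Preferred:** at t3 the carer self-completes the RUD and returns it to unmasked staff, unseen by the assessor.
- **Otherwise:** the RUD is given last at t3, after every other measure is scored and the assessor has completed the unmasking log for that visit.

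In either case, state that trial sessions are costed from the therapists' session logs described under Assessment of fidelity, which already record session length, and are not to be reported on the RUD. This also avoids counting the sessions twice.

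The cost is a sentence or two in each section and a change in form routing, with no added staff, visits or data. Self-completion carries a small risk of missing RUD items. Since the study sets out to examine completeness of the economic measures, unmasked staff should check the form on receipt.
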